### Sample size and power calculations and randomisation

Davies and colleagues report a meta-analysis of internet-based exercise intervention studies which suggests an average effect size of d = 0.14
[16]. A Cochrane review of general interventions to promote activity among inactive adults reports an average SMD = 0.28, but notes considerable heterogeneity in effects sizes
[4]. In the case of internet interventions aimed at reducing blood pressure, effects sizes of the order of SMD = 0.27 and 0.17 for systolic and diastolic blood pressure, respectively (equating to drops of 3.8 and 2.1 mmHg, respectively), have been identified in a recent meta-analysis
[35]. Based on these analyses, an effect size of 0.125 can be assumed for comparing means of MET-minutes per week and mmHg between the intervention and control arms (equinumerous) for a two-arm study. With this effect size, if each arm consists of 500 subjects, a power of 80% is obtained for a two-sided statistical contrast to show statistical significance, at the 5% level, of the difference of the means of the two arms with respect to these outcome variables. It is therefore decided that there will be 500 subjects in each of the four arms of the present study.

Block randomisation is to be conducted by the University of Surrey’s Clinical Research Centre. Participants cannot be blinded to the nature of the intervention they are receiving and for reasons of monitoring and contacting participants the research assistant also cannot be blinded. The primary analyst will be blinded to participant allocation.

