## Background

The health benefits of sport and physical activity (PA) have been studied extensively. The results demonstrate that participation in PA, which includes sporting activity, is associated with a reduced risk of over 20 health conditions, including cardiovascular disease and some cancers
[1, 2]. Targeting those with the greatest levels of inactivity will subsequently have an effect on all-cause mortality
[3] and produce the highest decrease in the incidence of chronic disease. In the most recent Cochrane review of interventions intended to increase physical activity
[4], the authors conclude that: "Nevertheless interventions which provide people with professional guidance about starting an exercise programme and then provide ongoing support may be more effective in encouraging the uptake of physical activity. There is no evidence that such interventions will reduce physical activity or cause other harm. There is only very limited evidence of the long-term effectiveness of interventions” (page 12).

Individuals report numerous barriers that impede their ability to be physically active
[5]. Lack of time and access to facilities are among the most common barriers that have been identified. “Exercise on prescription” interventions that involve a health professional’s written advice to a patient to be more physically active have been used with variable success
[6, 7]. A meta-analysis of the efficacy of gym-based exercise referrals for inactive people with medical conditions
[8] suggested that while these were effective the absolute health risk reduction was small due to patients failing to maintain activity levels over time. The authors show that, across the studies, 17 sedentary people would have to be referred for one person to become moderately active. They cite a range of barriers such as a lack of self-efficacy, poor body image, poor time management, lack of social support, intimidating environments, inadequate supervision and inconvenient opening hours as limiting the efficacy of these interventions.

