#### Sports exercise referral

The evidence of the effectiveness of interventions aimed at promoting sporting activity is of mixed quality. A recent Cochrane review reported that no controlled trials existed to assess the impact of sports interventions on sports participation
[20]; however, Cavill and colleagues in a review of studies with less restrictive design criteria (for example, controlled before and after studies) are able to point to a number of studies that show positive effects of structured sports training sessions on physical and sporting activity levels
[1]. They report nine studies in which sporting interventions have led to greater participation primarily through making activity enjoyable.

Underpinning theorising about the motivations to be active are notions of utility and hedonic calculus relating back to the 18th century ideas of Jeremy Bentham
[9, 21]. The basic assumption is that if exercise is pleasurable people will be more likely to repeat the experience and conversely if past experiences of exercise are unpleasant then the motivation to repeat the experience will be diminished. Although exercise is often promoted as having positive effects on mood it is far from clear that all people experience this positive outcome, particularly when pressed to exercise on gym equipment as is the case in GP exercise referrals. Indeed in the last decade or so a number of studies have shown that many people experience negative affective states, especially if they exercise at intensities approaching their ventilatory threshold
[22–25]. It has also been shown that even at intensities below the ventilatory threshold there is considerable variability in the degree of positive affect experienced during exercise which, in turn, has been implicated as a reason why activity levels remain low for many people.

The challenge is to associate exercise with other affective responses such as those resulting from success or socialising – hence an interest in linking activity to sport rather than repetitive activity on gym equipment. Several studies

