## Methods/design

Participants will be inactive people aged 18 to 74 years who are eligible to be referred by their GPs for an exercise intervention. Participants will be people with hypertension or high-normal blood pressure and assessed as being inactive or moderately inactive using the General Practice Physical Activity Questionnaire (GPPAQ) screening tool. The inclusion and exclusion criteria are detailed below.

The study will be conducted in the Guildford and Waverley CCG area (Surrey, UK) and patients will be recruited via GP surgeries serving catchment areas within reasonable reach of Surrey Sports Park and the five DC leisure centres in Waverley, Surrey, UK. We have designed the study with the intention to allow recruitment for all patients eligible for an exercise referral within the 9 months of the proposed trial data collection phase.

The trial design is shown in Figure 1. The key features are that, after a patient has been assessed as likely to benefit from an exercise intervention, their referral is to the project research assistant who will allocate the patient to one of four conditions on the basis of previous independent randomisation. These are: 1) GP gym-based referral (GPGR, the treatment as usual control); 2) GP gym-based referral plus web tool (GPGR + WEB); 3) sport referral at Surrey Sports Park (SPR); and 4) sport referral at Surrey Sports Park plus web tool (SPR + WEB). After obtaining informed consent patients attend a 12-week exercise programme (sport or gym) and their activity levels and sporting participation are monitored again at 6 months and 12 months after starting the exercise programme. Pending ethical approval the intention is to commence recruitment in the early autumn of 2013 for a period of 9 months.

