## Discussion

This randomised controlled trial compares GP referral to sport-based exercise with referral to the more conventional gym-based exercise programme. It hypothesises that enjoyment, choice and therefore some degree of control might result in greater persistence. It is needed because, currently, such a small proportion of people referred for exercise persist. The challenges for this trial include recruiting sufficient numbers to the trial, and matching those who are recruited to appropriate exercise-based interventions. We need to recruit 2,000 patients and we need to provide those allocated to sports-based exercise activities at a time and of a type that they might opt to participate in. There are many uncertainties as to the feasibility of this, which will be tested in the course of this study.

Further parallel work is required to explore change in vascular risk and the potential cost effectiveness of sport-based exercise interventions. The trial is not looking at overall cardiovascular risk, or change in risk score (such as Framingham or QRisk score), nor at major cardiovascular outcomes and death. The former may be required in order to carry out a cost-effectiveness analysis. The latter would provide data on the safety of referral for sport-based exercise programmes and also about any change in health outcomes, though the scale of the trial and duration of follow-up would not provide sufficient data for any difference to be detectable between arms.

The theoretical framework around the importance of enjoyment and control potentially leading to greater persistence with sport-based, compared to gym-based, exercise may be challenged if we find no difference between arms.

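### The single effect size of 0.125 has no stated basis for sport versus supervised gym exercise, so the 80% power is unsupported for that contrast, and non-significance alone would be weak evidence against the theory

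*Protocol article*

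**What the plan says.** The section on sample size, power and randomisation cites three reviews: internet-based exercise interventions (d = 0.14), general interventions to promote activity in inactive adults (SMD = 0.28, with considerable heterogeneity) and internet interventions for blood pressure (SMD = 0.27 systolic, 0.17 diastolic). It then states: "Based on these analyses, an effect size of 0.125 can be assumed for comparing means of MET-minutes per week and mmHg". It continues that "if each arm consists of 500 subjects, a power of 80% is obtained for a two-sided statistical contrast", with significance judged "at the 5% level, of the difference of the means of the two arms". This two-arm result is carried over to all four arms, at 500 each.

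Methods/design names the comparator as "GP gym-based referral (GPGR, the treatment as usual control"). Both the sport and the gym programme last 12 weeks, and the Background says a qualified exercise professional supervises sport as well as gym referral. The section on research questions and hypotheses calls a new intervention successful on its own at an average gain of 100 MET-minutes per week, and superior to gym referral at 20.

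The section on sports exercise referral reports a review finding that "no controlled trials existed to assess the impact of sports interventions on sports participation". The Discussion says the enjoyment and control framework "may be challenged if we find no difference between arms".

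**The concern.** A power statement is only as good as the difference it assumes. The trial asks whether sport does better than an active, supervised programme that the article itself regards as effective, though with a small absolute benefit. The cited effects come from other kinds of intervention. Only the web add-on contrast (GPGR + WEB versus GPGR) has a source that resembles its question. For sport versus gym, 0.125 is borrowed without being said to be.

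Two things are at stake. A reader will believe that sport versus gym has 80% power when nothing in the document supports that. And the Discussion proposes to read no difference between arms as a possible challenge to the theory. If the contrast has low power for the differences that matter, a non-significant result says little about the theory.

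**Working it through.** **Inputs.** From the sample size section: d = 0.125, 500 per arm, two-sided 5%, stated power 80%. From the research questions: targets of 100 and 20 MET-minutes per week. That section and the sample size section give no SD, so SDs below are assumptions.

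**1. The stated power.** For two equal arms, power = Φ(d√(n/2) − 1.96) + Φ(−d√(n/2) − 1.96).
- d√(n/2) = 0.125 × √250 = 1.976. Power = Φ(0.016) = 0.507, or about 51%. The 80% does not reproduce.
- For 80%: n = 2 × (1.96 + 0.84)² / 0.125² = 1,005 per arm.
- Other readings: a one-sided test gives 63%. ANCOVA reaches 80% only with a baseline correlation of about 0.71, which is not stated (0.5 gives 63%). Pooling over the web factor, 1,000 versus 1,000, gives 79.8%, but the section describes two arms of 500. The one-sample formula, (2.80/0.125)², gives about 502, so a missing factor of 2 is a possible explanation.

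**2. Detectable difference at 80% power.** 2.80 × √(2/500) = 0.177 for 500 versus 500; 2.80 × √(2/1,000) = 0.125 for 1,000 versus 1,000.

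**3. Sources set against contrasts.**

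| Contrast | Cited evidence of the same kind |
|---|---|
| GPGR + WEB v GPGR | Internet reviews (0.14; blood pressure 0.27/0.17) |
| SPR v GPGR | None described |
| SPR + WEB v GPGR | Internet reviews, for the web part only |

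**4. Power over an assumed range, 500 versus 500.**

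| d | Power | n per arm for 80% |
|---|---|---|
| 0.125 | 51% | 1,005 |
| 0.10 | 35% | 1,570 |
| 0.0625 | 17% | 4,019 |
| 0.05 | 12% | 6,280 |

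The values below 0.125 are illustrations; the document gives none for this contrast.

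**5. Link to MET-minutes.**
- If 0.125 stands for 20 MET-minutes, the SD is 20/0.125 = 160.
- If 0.125 stands for 100 MET-minutes, the SD is 100/0.125 = 800. Then 20 MET-minutes is d = 20/800 = 0.025, and power is Φ(0.395 − 1.96) + Φ(−0.395 − 1.96) = 0.059 + 0.009, about 7%.

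**6. What a null result could exclude.** The 95% interval has a half-width of 1.96 × √(2/500) = 0.124 SD (0.088 SD for 1,000 versus 1,000). With an observed difference of exactly zero, it excludes 20 MET-minutes only if the SD is below 20/0.124, about 161. With no true difference, the chance that the interval excludes 20 is Φ(20/(SD × √(2/n)) − 1.96):
- SD 800: about 6% for 500 versus 500, 8% pooled.
- SD 160: about 51% for 500 versus 500, 80% pooled.

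**The case against.** The case for the authors has weight. The value 0.125 lies below every cited effect and is less than half of the 0.28 for general interventions. With no direct trials of sport to draw on, borrowing an effect was unavoidable. The article also calls the absolute benefit of gym referral small. These points stand, but they do not make 0.125 evidence for sport versus gym: the section mentions no allowance for the control, and 0.125 is only 11% below the 0.14 for internet exercise interventions.

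Several stronger readings are tempting, and the document does not support them.

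- **That the reviews measured benefit against lesser care.** Their control groups are not described. A mismatch of comparators is a reasonable inference, not something shown.
- **That 0.28 is what the gym arm already gains.** The Background says that, within that review, "interventions which provide people with professional guidance about starting an exercise programme and then provide ongoing support may be more effective". This singles out a subset; it does not tie the average of 0.28 to gym referral.
- **That the gym arm's own effect can be subtracted.** The Background says "17 sedentary people would have to be referred for one person to become moderately active", which might be converted to a standardised effect and taken from 0.28. That needs an assumed rate of activity without referral and mixes two reviews. At assumed rates of 30% to 50% it leaves about 0.12 to 0.13, close to the planned value. It proves nothing either way.
- **That sport could be moderately better and still probably be missed.** At d = 0.18, 500 versus 500 has about 80% power. Non-significance is the likelier outcome only for differences below about 0.125.
- **That a null result cannot challenge the theory.** The Discussion says only that it may, and an interval that excluded a worthwhile difference would be informative.

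**Conclusion.** The point holds in a limited form. The 80% power is unsupported for sport versus gym because no cited source is described as addressing that contrast, and the sample size section does not carry over the smaller target that the research questions set against gym. The fault is an unjustified assumption, not a demonstrated overestimate.

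On size: even if 0.125 is accepted, power is about 51% for 500 versus 500. That is a separate arithmetic error, and correcting it alone would leave the effect size without a basis. Below 0.125, power drops quickly. What the design offers for 20 MET-minutes depends on an SD that the sample size section does not give: about 51% power at an SD of 160, about 7% at 800. These figures assume equal arms of 500 fully observed, the normal approximation, and no gain from baseline adjustment.

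Non-significance alone would therefore be weak evidence against the enjoyment and control theory.

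**What to change.** In the sample size section:

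1. Say that the evidence behind 0.125 bears mainly on the web add-on contrast, and that 0.125 is an assumption for sport versus gym.
2. Replace the 80% claim with the detectable difference: d of about 0.18 at 80% power for 500 versus 500, and 0.125 only for 1,000 versus 1,000 pooled over the web factor. Pooling estimates one sport effect across both web conditions, so it sits awkwardly with the aim of testing synergy unless that is addressed.
3. Give power over a stated range for sport versus gym, such as 51%, 35%, 17% and 12% at 0.125, 0.10, 0.0625 and 0.05.
4. State the SD that links 0.125 to the 20 MET-minute target.

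In the Discussion:

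5. Do not treat non-significance alone as a challenge to the theory. Report the 95% confidence interval for sport minus gym. Call the theory challenged only if the interval excludes the protocol's own superiority difference, and otherwise report the result as inconclusive.
6. Warn that, with a half-width of about 0.124 SD, inconclusive will be the usual result of a null trial unless the SD is small.

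The cost is wording in one section and one interpretation rule, with no extra patients. The power statement becomes less favourable, and the authors must accept that a null trial may settle little.

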#### Research questions and hypotheses

The primary purpose of the trial is to test the independent and synergistic efficacy of the 12-week sports-oriented exercise referral intervention and the self-help web-based intervention intended to promote sustained and increased levels of physical activity over a period of 12 months. Do these interventions separately and in combination improve these indicators and do they improve them above that expected by existing gym-based GP referral alone? The secondary questions are whether these interventions improve other clinical indicators of cardiovascular health (for example, body mass index, waist and hip measures, blood pressure and other measures that contribute to the QRisk2 risk indicator) above that expected by existing gym-based GP referral? Do these interventions increase participation in sporting activity over a period of 12 months?

The interventions individually will be regarded as successful if they lead to an average increase in activity of 100 metabolic equivalent of task (MET)-minutes per week. This equates to engaging in an extra moderate intensity activity, say brisk walking (3.3 MET) for 30 minutes per week. The new interventions will be regarded as superior to the standard gym-based referral if they increase activity levels above those of the standard care gym-based exercise by 20 MET-minutes per week.

We will assess changes in indicators relating to cardiovascular health including blood pressure, weight, and waist and hip circumference. In terms of blood pressure, the interventions will be regarded as successful if they lead to an average decrease in blood pressure of 2.5 mmHg. We will assess the proportion of the sample reducing their blood pressure by more than 10 mmHg and an intervention will be regarded as a success if more than 20% of the members of that study arm achieve a reduction greater than this. The interventions will also be deemed to have been successful in promoting sports participation if they increase sports-related activity by 100 MET-minutes per week.

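### The blood pressure power claim is made at effect size 0.125, about 1.5 to 1.8 mmHg on the protocol's own figures; that difference has about 51% power, not 80%, and is not reconciled with the 2.5 mmHg success criterion

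*Protocol article*

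**What the plan says.** The section on sample size, power and randomisation of the protocol article uses one standardised effect for two outcomes: "an effect size of 0.125 can be assumed for comparing means of MET-minutes per week and mmHg between the intervention and control arms". It then claims that "if each arm consists of 500 subjects, a power of 80% is obtained"; the test meant is two-sided at 5% and compares two arm means. On that basis it settles that "there will be 500 subjects in each of the four arms of the present study". Among the sources for the effect size it cites "effects sizes of the order of SMD = 0.27 and 0.17 for systolic and diastolic blood pressure, respectively", and it puts these on the mmHg scale as "equating to drops of 3.8 and 2.1 mmHg, respectively".

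The section on research questions and hypotheses sets the blood pressure target in other units: "the interventions will be regarded as successful if they lead to an average decrease in blood pressure of 2.5 mmHg". It names neither a comparator nor systolic or diastolic pressure. The section on intervention effectiveness plans t-tests and baseline-adjusted analysis of covariance against the control arm for activity, and similar analyses for the secondary outcomes.

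The article nowhere expresses 0.125 in mmHg or relates it to 2.5 mmHg.

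**The concern.** Blood pressure is explicitly inside the power claim, so a reader will take the 80% as describing what the trial can show on blood pressure. The paragraph supplies enough to turn 0.125 into mmHg, and the result is well below the article's own success threshold. The power statement and the success rule therefore concern different differences. The 80% is also not what the stated inputs give.

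At stake is how the blood pressure results are read. A significant between-arm difference of about 1.8 mmHg would count as a positive contrast yet fall short of 2.5 mmHg if the criterion were applied to that contrast, and the article does not say which result governs. A non-significant result would be read against a stated power that the design does not have at 0.125.

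**Working it through.** **Inputs, all from the protocol article.** Effect size 0.125; 500 per arm; two-sided 5%; stated power 80%; SMD 0.27 = 3.8 mmHg systolic; SMD 0.17 = 2.1 mmHg diastolic; success threshold 2.5 mmHg. No dropout allowance is stated, so 500 is taken as the number analysed.

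**1. The stated power.** For two equal arms, power = Φ(d/√(2/n) − 1.96).
- d/√(2/n) = 0.125/√(2/500) = 0.125/0.0632 = 1.976.
- Power = Φ(1.976 − 1.96) = Φ(0.016) = 0.507; the t distribution gives 0.506. The printed 80% is not reproduced.
- The n needed for 80% is 2 × (1.96 + 0.842)²/0.125² = about 1,005 per arm.
- About 80% (79.8%) appears with 1,000 per group, or with a one-sample formula on 500: Φ(0.125 × √500 − 1.96) = Φ(0.835). The second is what results if the factor of 2 for a two-arm comparison is left out. Neither is the contrast described.
- A one-sided test gives 63.0%. Baseline adjustment reaches 80% only at a baseline correlation of about 0.71, which is not stated.

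**2. Converting 0.125 to mmHg.** SD = mmHg drop/SMD. Ranges allow for rounding of the printed figures (SMD ± 0.005, mmHg ± 0.05).

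| | Systolic | Diastolic |
|---|---|---|
| Implied SD | 3.8/0.27 = 14.07 | 2.1/0.17 = 12.35 |
| 0.125 in mmHg | 1.76 (1.70–1.82) | 1.54 (1.46–1.63) |
| 2.5 mmHg as an effect size | 2.5/14.07 = 0.178 | 2.5/12.35 = 0.202 |

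Rounding does not close the gap to 2.5 mmHg.

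**3. Power for a true between-arm difference of 2.5 mmHg, 500 analysed per arm.** SE = SD × √(2/500).
- Systolic: SE = 0.890; 2.5/0.890 = 2.81; Φ(2.81 − 1.96) = 0.80 (0.78–0.83 over rounding). 80% needs 498 per arm.
- Diastolic: SE = 0.781; 2.5/0.781 = 3.20; Φ(3.20 − 1.96) = 0.89 (0.86–0.92). 80% needs 384 per arm.

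The difference detectable with 80% power at 500 per arm is (1.96 + 0.842) × √(2/500) = 0.177 SD, that is 2.49 mmHg systolic or 2.19 mmHg diastolic.

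**4. Sensitivity to the SD.** The trial's own SD is not given. The last three rows are illustrative assumptions; all use the formula of step 3.

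| SD (mmHg) | 0.125 in mmHg | Power for 2.5 mmHg |
|---|---|---|
| 12.35 | 1.54 | 89% |
| 14.07 | 1.76 | 80% |
| 16 | 2.00 | 70% |
| 18 | 2.25 | 59% |
| 20 | 2.50 | 51% |

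At an SD of 20 the two differences coincide, but the power is then 51%. The power at 0.125 is 51% whatever the SD.

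**The case against.** The strongest case is that no contradiction has been shown. The 80% is tied to statistical significance of a difference in means; the article never promises an 80% chance of meeting the 2.5 mmHg rule. Planning on an effect smaller than the success threshold is not in itself an error, since power for the larger difference is higher. Both points stand.

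A reader might infer two stronger conclusions, and the document supports neither. The first is that the trial is underpowered for 2.5 mmHg; step 3 shows otherwise on the implied SDs. The second comes from computing the chance that the observed difference reaches 2.5 mmHg when the true effect is 0.125 and setting that against the printed 80%. These are different quantities: the chance of observing at least the threshold is only 50% even when the true difference equals it.

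The success rule also reads most naturally as a fall within an arm. For activity, the same section separates an average gain (100 MET-minutes) from superiority over gym referral (20 MET-minutes), and the blood pressure rule follows the first form. Because the control is itself an exercise programme, a 2.5 mmHg fall within an arm and a 1.5 to 1.8 mmHg difference between arms could both occur. This stands too. It means that the printed power cannot be the power for the rule as written, which supports reconciling the two.

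Lastly, the SDs are back-calculated from a cited meta-analysis and are not this trial's. That stands as a limit on the mmHg figures, but it does not affect the 51%.

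**Conclusion.** The point holds as an unreconciled mismatch together with a wrong power figure. With 500 analysed per arm and two-sided 5%, an unadjusted comparison at 0.125 has about 51% power, not 80%. On SDs of about 14.1 and 12.4 mmHg, assumed to carry over to this trial, 0.125 is about 1.8 mmHg systolic or 1.5 mmHg diastolic, 30% and 38% below 2.5 mmHg (1 − 1.76/2.5 and 1 − 1.54/2.5). The power statement and the success criterion therefore refer to different quantities.

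The planned size looks adequate for a 2.5 mmHg between-arm difference (about 80% and 89%), provided the SD is not materially larger than assumed and 500 per arm are analysed. Blood pressure is a secondary outcome, so this should be corrected but does not threaten the trial. The wrong power figure also applies to MET-minutes, the primary outcome, where it weighs more and needs its own correction; rewording the blood pressure statement does not settle it.

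**What to change.** **Sample size section.** Stop using the shared 0.125 for blood pressure and state instead: 'For a between-arm difference of 2.5 mmHg, 500 analysed per arm gives about 80% power (systolic, assumed SD 14.1 mmHg) and 89% (diastolic, assumed SD 12.4 mmHg) at two-sided 5%.' Say where the SDs come from and show the sensitivity to them.

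**Hypotheses section.** Name the blood pressure component to which 2.5 mmHg applies. Judge the criterion from the baseline-adjusted difference against GPGR, with its confidence interval, so that it uses the controlled contrast already planned.

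**If 0.125 is kept for blood pressure.** State its mmHg equivalent (about 1.8 systolic, 1.5 diastolic), its power of about 51% at 500 per arm, and that this is not the power for the 2.5 mmHg criterion.

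**Cost.** No extra patients or measurements. The stated detectable effect becomes larger (0.18 to 0.20 instead of 0.125). Tying 2.5 mmHg to the between-arm difference is more than an edit: it changes the criterion from its most natural within-arm reading, so it should be recorded as a deliberate change.

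### The stated 80% power does not follow from its own inputs: 500 per arm at an effect size of 0.125 gives about 51%

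*Protocol article*

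**What the plan says.** The section on sample size, power and randomisation in the protocol article reviews published effects of d = 0.14 for internet exercise interventions, SMD = 0.28 for general activity interventions, and SMD = 0.27 and 0.17 for systolic and diastolic blood pressure. From these it concludes that "an effect size of 0.125 can be assumed for comparing means of MET-minutes per week and mmHg between the intervention and control arms", with equal arms in a two-arm study. It continues: "With this effect size, if each arm consists of 500 subjects, a power of 80% is obtained for a two-sided statistical contrast". The test is specified as "at the 5% level, of the difference of the means of the two arms".

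The section then sets 500 subjects for each of the four arms on this basis. The Discussion carries the total forward: "We need to recruit 2,000 patients". The section on intervention effectiveness plans to compare the intervention arms with the control arm by t-tests and by analysis of covariance with baseline activity as the covariate.

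**The concern.** Every input needed to check the power is stated, and together they do not give 80%. An effect of 0.125 is small, and two arms of 500 are about half of what a two-sample comparison needs to detect it. The stated number is close to what the one-sample (or paired) formula gives, which suggests that the variance of only one mean was counted.

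The 80% figure is the justification for the size of the whole trial, and readers will use it to interpret the result. If power is really about 51%, a non-significant arm-versus-control difference is weak evidence that the arms do not differ. The Discussion remarks, in hedged terms, that a finding of no difference could call the theory of enjoyment and control into question. A reader who believed the 80% would give such a finding more weight than the design supports.

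**Working it through.** **Inputs, all from the sample size section:** effect size d = 0.125; n = 500 per arm; equal allocation; two-sided α = 0.05, so z = 1.960; target power 80%, so z = 0.842. No baseline correlation, pooling of arms or dropout allowance enters the stated calculation.

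**1. Power of the contrast as described (two independent means).**
Power = Φ(d·√(n/2) − 1.960) = Φ(0.125 × √250 − 1.960) = Φ(1.976 − 1.960) = Φ(0.016) = 50.7%. The noncentral t calculation gives 50.6%. The stated 80% is not reproduced.

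**2. Sample size for 80% power.**
n per arm = 2(1.960 + 0.842)²/0.125² = 2 × 7.849/0.015625 ≈ 1,005 (1,006 by the t distribution). Over four arms that is 4 × 1,005 = 4,020, against the planned 2,000.

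**3. Effect detectable with 80% power at 500 per arm.**
d = (1.960 + 0.842) × √(2/500) = 2.802 × 0.0632 = 0.177. This exceeds two of the effects the section cites, 0.14 and 0.17. At d = 0.14 the unadjusted power is 60%, and at d = 0.17 it is 77%.

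**4. Where 500 may come from.**
Without the factor 2, n = 7.849/0.015625 = 502, and power at n = 500 is Φ(0.125 × √500 − 1.960) = Φ(0.835) = 79.8%. This matches the article's figures closely, but it is the formula for one mean.

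**5. Other readings tried (500 per arm and d = 0.125 unless stated).**

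| Reading | Power |
|---|---|
| One-sided 5% | 63.0% |
| Control arm (500) against the other three pooled (1,500) | 67.7% |
| Bonferroni for three comparisons | 33.8% |
| ANCOVA, assumed baseline correlation 0.3 / 0.5 / 0.6 | 54% / 63% / 70% |
| Pooled halves of the 2×2 layout, 1,000 v 1,000 | 79.8% |
| 0.125 read as Cohen's f (d = 0.25), 500 in total | 79.7% |
| 0.125 read as Cohen's f (d = 0.25), 500 per arm | 97.7% |

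The correlation at which ANCOVA reaches 80% is √(1 − (0.125/0.177)²) ≈ 0.71. A change-score analysis would need about 0.75 (79.8%).

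**6. Sensitivity to loss.** The 50.6% assumes that all 500 per arm are analysed at 12 months. If, as an assumption, 400 or 350 per arm were analysed, power would be 42% or 38%.

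**The case against.** No one disputes the arithmetic of the two-arm contrast. The objections bear on what surrounds it.

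- **The cause is inferred.** The article shows no formula. Pooled margins of 1,000 v 1,000, or Cohen's f with 500 in total, also land near 80%. This stands, so the missing factor 2 should be called likely and not proven. Neither alternative rescues the sentence. The text puts 500 in each arm and tests a difference between two arms, and 0.125 is derived from values labelled d and SMD. If it were Cohen's f, 500 per arm would give 97.7%, and the stated 80% would still be wrong.
- **ANCOVA is planned, and 51% is the unadjusted figure.** This is fair: adjustment would raise power to between 54% and 70% for assumed correlations of 0.3 to 0.6. That still falls short of 80%. No correlation is stated, and plain t-tests are planned alongside.
- **Power is higher at the larger cited effects.** At 0.27 and 0.28 it is about 99%. But the protocol chose 0.125 as its design value and attached the 80% to it.
- **An attrition allowance may sit in the full protocol.** This also stands. The absence of one from a condensed article is not counted here, and the 400 and 350 figures above are illustrations under assumed losses.
- **The Discussion remark is tentative and concerns theory.** That is so. It shows how a null result might be read and does not commit the authors to a conclusion.

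**Conclusion.** The concern holds and must be corrected. With the stated inputs the power is 50.6%, not 80%, an overstatement of about 29 percentage points. The type II error is about 49% instead of 20%. The conclusion rests on 0.125 being a standardised mean difference, as its derivation implies, on an unadjusted two-sided 5% test, and on all 500 per arm being analysed. No reading consistent with the text restores 80%. The only route within the planned analyses is a baseline correlation of about 0.71, which the article does not state.

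**What to change.** Replace the power statement with figures that follow from the inputs. With 500 analysed per arm and a two-sided 5% test, power for an arm-versus-control contrast is about 51% at d = 0.125, and 80% power is available for d of about 0.177. Give the same figures at the number expected to be analysed at 12 months. If the 80% relied on an unstated assumption, such as a baseline correlation or a different effect-size scale, state and justify it and show the calculation.

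The cost is a change of wording in the protocol and in any analysis plan that repeats the figure. No patients are added and the analysis is unchanged, but the declared power for single-arm contrasts becomes less favourable.

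Making sport v gym and web v no web the primary contrasts would give 79.8% at 0.125 with 1,000 analysed per side. That is a separate design decision and is not needed for this correction. It changes the primary question in a trial already recruiting, relies on there being little interaction between the two interventions, and leaves the arm-versus-control questions at the lower power.
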